#### Patient safety indicator

We will evaluate whether the intervention appears to increase adverse events; for example, because of antibiotics being withheld for appropriate conditions more frequently due to the intervention, by creating and evaluating an indicator of unintended harms. To do this we will use the EMR to track whether any patients subsequently become hospitalised in any hospital in the Shaoguan Prefecture, including its county- and prefectural-level teaching hospitals, due to respiratory infections or sepsis, within 30 days of their index visit to a participating township hospital during the trial period. This will allow us to calculate a cluster-level hospitalisation rate for trial participants as the number of hospitalisations for respiratory infections or sepsis per 100 outpatient consultations. We will compare both patient safety indicators between treatment arms.

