## Background

Inappropriate use of antibiotics is a major contributor to the global public health challenge of antimicrobial resistance, and has been widely documented in the world, especially in low- and middle-income countries (LMICs) [1, 2]. Rising levels of antimicrobial-resistant infections may devastate our health system, costing many lives and using valuable resources [3, 4]. Acute respiratory infections (ARIs) are commonly seen in primary care consultations, with upper respiratory tract infections (URTIs) accounting for the largest source of inappropriate antibiotic use [5, 6]. This is because most URTIs are viral and self-limiting, and the administration of antibiotics is not clinically effective at shortening duration or symptom severity [7]. Similarly, among lower respiratory tract infections (LRTIs), acute bronchitis is commonly viral, but up to 80% of acute bronchitis patients still receive antibiotics [8]. Bacterial respiratory infections in primary care include acute otitis media, acute sinusitis and group A streptococcal pharyngitis and pneumonia, where narrow-spectrum antibiotics should be recommended as the first choice according to US [9] and UK guidelines [10]. However, broad-spectrum antibiotics, such as macrolides and fluoroquinolones, are often given which are more likely to generate resistance [11–13].

In China, inappropriate use of antibiotics is rampant and has raised national attention. This is particularly challenging in rural areas, as rural health workers have less education/training and may inappropriately prescribe more frequently [14]. A cross-sectional study in 10 provinces in Western China showed that antibiotics accounted for over half of the total prescriptions issued, and mostly for ARIs [15]. China has issued policies to regulate the use of antibiotics over the past 10 years. In 2012, the Chinese MoH issued a regulation for antibiotic prescriptions, limiting them to less than 60% of all prescriptions for inpatients and 20% for outpatients [16]. However, no operational details have been given. The policy has not been proven effective at improving appropriate antibiotic prescribing [17]. Additionally, the policy only focussed on large hospitals and neglected primary care facilities [18, 19].

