#### Patients

Our trial targets township hospitals, which provide the majority of primary care in rural China. Thus, we will collect all outcome data from eligible patients’ prescriptions issued within participating township hospitals. Similar to our previous trial setting, all outpatient consultations in China result in a prescription due to the request of health insurance scheme for documenting the consultation and the routine practice to give patients medications/herbs after the consultation. We will not collect prescriptions from village doctors because there is not sufficient documentation (such as prescriptions) available in private village clinics. We define eligible patients as outpatients aged between 0 and 75 years who receive a primary diagnosis of an ARI and receive a prescription following their consultation with a family physician in a township hospital. This includes a diagnosis of any URTIs according to the *International Classification of Disease, version 10* (ICD-10), and acute bronchitis as an uncomplicated acute lower respiratory tract infection (LRTI) (Table 1). However, patients and their prescriptions will not be eligible for inclusion in the trial if they are high-risk patients diagnosed with either: (1) non-ARIs, (2) pneumonia, as it is severe and clinically challenging to group with other uncomplicated ARIs (but we will extend the invention in the future to include pneumonia), (3) chronic conditions including asthma, chronic obstructive pulmonary disease, non-infective or non-acute disorders (e.g. cystic fibrosis, pulmonary embolus, heart failure, oesophageal reflux and/or allergies), non-respiratory infections (e.g. cutaneous infections, urinary tract infections, trauma-related infections, bacterial enteritis and/or cellulitis/abscess), immunological deficiencies, tuberculosis or any form of cancer.

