**Fig. 1 Fig1:**
[figure not shown]
Detailed trial timeline. *Enrolment includes participating township hospitals signing the consent form and relevant healthcare staff being trained

**Table 1 Tab1:** *International classification of Diseases, version 10* (ICD-10) codes used for acute respiratory infection case definitions

Acute respiratory infections	ICD-10 codes
Acute nasopharyngitis (common cold)	J00
Acute pharyngitis	J02.8, J02.9
Acute tonsillitis	J03.8, J03.9
Acute URTIs of multiple and unspecified sites	J06
Acute bronchitis	J20
Acute sinusitis	J01.0, J01.1, J01.2, J01.4, J01.9
Acute otitis media	H65, H66, H67
Streptococcal pharyngitis	J02.0
Streptococcal tonsillitis	J03.0

*URTIs* upper respiratory tract infections

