#### Patient safety indicators

We will collect all inpatient charts from the EMR managed under the Prefectural Health Information Centre for any patients who are hospitalised (in any hospital within the Shaoguan Prefecture, including its county and prefectural-level teaching hospitals) within 30 days of their index visit to a trial township hospital for an ARI or for sepsis. The Prefectural Health Information Centre will provide de-identified patient charts for review after identifying patients as having visited a trial township hospital within 30 days of becoming hospitals, using patients’ encrypted insurance numbers. We will then have these inpatient charts reviewed by a group of three to five physicians (blinded to the township hospital of all patients) who will decide if the hospitalisation is due to one of the following reasons: (1) not providing antibiotics during the index visit; (2) other inappropriate usage of antibiotics, such as prescribing the wrong antibiotics; (3) side-effects from antibiotics or other medications and (4) undetermined. Any patients who are determined to have been hospitalised due to either the first or second of these reasons will be included in the calculation of the adverse events’ outcome.

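### The patient safety indicator counts and reviews only admissions for respiratory infection or sepsis, so it may miss focal and post-infectious complications of the bacterial ARIs that the trial enrols

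*Protocol article*

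**What the plan says.** In the Protocol article, *Outcomes – Patient safety indicator* sets up a check on whether the intervention increases adverse events. It gives as an example harm arising "because of antibiotics being withheld for appropriate conditions more frequently due to the intervention". The events counted are admissions "due to respiratory infections or sepsis, within 30 days of their index visit to a participating township hospital during the trial period", summarised per cluster as "the number of hospitalisations for respiratory infections or sepsis per 100 outpatient consultations".

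*Data collection and management – Patient safety indicators* describes the chart review. Charts are collected for patients hospitalised "within 30 days of their index visit to a trial township hospital for an ARI or for sepsis". Three to five physicians, blinded to township hospital, assign each admission to one of four reasons. The first is that no antibiotic was given at the index visit; the second is other inappropriate antibiotic use. "Any patients who are determined to have been hospitalised due to either the first or second of these reasons" enter the adverse-event outcome.

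Table 1 lists the enrolled diagnoses. They include acute sinusitis (J01 codes), acute otitis media (H65–H67), "Streptococcal pharyngitis" (J02.0) and streptococcal tonsillitis (J03.0). The Background states: "Bacterial respiratory infections in primary care include acute otitis media, acute sinusitis and group A streptococcal pharyngitis and pneumonia". The *Intervention* section counts amoxicillin or penicillin as appropriate for bacterial pharyngitis, sinusitis, otitis media and bronchitis.

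**The concern.** The indicator should be able to register harm in the diagnoses where withholding an antibiotic could plausibly do harm. For bronchitis, an admission for respiratory infection or sepsis is a natural endpoint. For ear, sinus and streptococcal throat infection it fits less well. When these go wrong, the admission may be for a focal infection outside the airways or for a post-infectious illness.

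The gap lies upstream of adjudication. Charts are selected by cause of admission before the panel sees them, so careful blinded review cannot recover what the filter leaves out, and a later analysis plan cannot analyse charts that were never requested.

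What is at stake is how a null safety result is read. A reader could take it as reassurance across all enrolled ARIs, when it would say less about some of the diagnoses for which the trial itself regards antibiotics as appropriate.

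**Working it through.** The documents give no event rate, margin or power for the indicator, so there is no figure to reproduce. The check is a comparison of sections.

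1. **Causes counted.** *Outcomes* gives respiratory infection or sepsis. *Data collection* gives ARI or sepsis. The intervention-arm alarm in Table 2 and the fourth strength in the Discussion also use respiratory infection or sepsis.

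2. **What the filter in *Data collection* qualifies.** Its final words could grammatically attach to the index visit instead of the admission. That reading would widen the charts to any cause, but it does not fit: sepsis is not a Table 1 diagnosis, and *Outcomes* fixes the cause of the admission.

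3. **Diagnoses enrolled for which antibiotics can be appropriate.** Otitis media, sinusitis, streptococcal pharyngitis and streptococcal tonsillitis are four of the nine rows of Table 1. This counts rows, not patients; the diagnosis mix is not given.

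4. **Complications against the filter.** The documents list no complications, so this step rests on general clinical knowledge. Mastoiditis, meningitis, orbital or intracranial infection, rheumatic fever and glomerulonephritis are in general neither respiratory infection nor sepsis. Cases that progress to sepsis or pneumonia, admissions for the index infection itself where it is classed as respiratory, and throat abscesses that coders treat as respiratory would still count.

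5. **Any other outcome that would catch them.** None of the nine secondary outcomes does; they cover prescribing content and cost.

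6. **Whether the data source forces the restriction.** It does not. The Discussion expects the integrated system to yield all hospitalisation data in the prefecture.

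7. **Whether the gap is acknowledged.** The limitation on the safety indicator mentions only patients who do not reach hospital because of cost.

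**Illustration of size.** Let E be the true excess of complication admissions in the intervention arm and s the share with a cause outside the two counted. The excess seen is (1 − s) × E. Neither E nor s is in the documents. Assuming E = 10:

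| s (assumed) | Excess seen |
|---|---|
| 25% | 0.75 × 10 = 7.5 |
| 50% | 0.50 × 10 = 5 |
| 75% | 0.25 × 10 = 2.5 |
| 100% | 0 × 10 = 0 |

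If E = 0 for these diagnoses, nothing is lost, whatever s is.

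**The case against.** The best defence is that a specific admission rate paired with blinded attribution is a reasonable design. A wider list adds very rare events with different timing to an indicator that has no stated power, and code lists often sit in a fuller document. Part of this stands: it argues for leaving the existing indicator as it is and adding a separate count. It does not remove the gap, because the restriction by cause is stated in the article itself and is more than a missing code list.

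A reader might also infer four stronger points that the documents do not support.

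- *That the indicator cannot detect complications of these infections.* Some still count, as set out in step 4 of the working. Nor is withheld treatment its only purpose; the protocol offers that as an example.
- *That pneumonia admissions drop out because Table 1 has no pneumonia code.* The Abstract, Background and primary outcome each name pneumonia as an exclusion from ARI, which implies that the term otherwise includes it. Table 1 defines enrolled prescriptions, and nothing ties it to admissions. What remains is a difference of wording to reconcile.
- *That the protocol itself classes abscess as non-respiratory.* The phrase "non-respiratory infections (e.g. cutaneous infections, urinary tract infections, trauma-related infections, bacterial enteritis and/or cellulitis/abscess" belongs to a list of patient exclusions. It does not classify admissions and cannot settle how a throat abscess would be ruled.
- *That the safety result is biased towards no harm.* This requires less antibiotic use in the bacterial ARIs in the intervention arm. The training teaches that antibiotics are appropriate there, which works against it. Spill-over is possible, since the primary outcome counts any antibiotic in any enrolled diagnosis, but its size is not shown.

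**Conclusion.** The point holds as a limitation of coverage that should be repaired. Focal and post-infectious complications of otitis media, sinusitis and streptococcal throat infection may fall outside both the admission rate and the chart review, and no other outcome picks them up. A null result would give limited reassurance for these diagnoses. It could be biased towards no harm if the intervention also reduces antibiotic use in them.

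The size cannot be stated: the documents give no diagnosis mix, complication rate or share outside the two causes. The conclusion assumes that complications of the kinds named are usually admitted under causes other than respiratory infection or sepsis, which is general clinical knowledge and not something the protocol says. It does not touch the primary outcome or its sample size.

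**What to change.** - Keep the current indicator and its blinded attribution.
- Use one admission wording in both safety sections: respiratory infection, stated to include pneumonia, or sepsis.
- Add a pre-specified supplementary count, reported by arm and separately from the main indicator, of 30-day admissions for listed complications of the Table 1 diagnoses. The list could include mastoiditis, meningitis, orbital and intracranial infection, rheumatic fever and glomerulonephritis. All-cause 30-day admission is a simpler alternative.
- Send the listed-complication charts to the same blinded panel.
- State the remaining gap beside the existing limitation on patients who do not reach hospital.

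The cost is a wider query of inpatient records that the Prefectural Health Information Centre already searches, and a few more charts for the panel. The added events will be rare, so the count will have little power and should be presented descriptively.

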### Sample size

Our sample size is calculated based on our primary APR outcome. Previous exploratory work suggested the existing township hospital APR level to be around 80%. We assume that the treatment will reduce the intervention arm APR by more than 15 percentage points during the trial period, based on how effective the previous related trial was [25], which is viewed as the minimum clinically important effect in the context of the extremely high existing APR levels. Based on our previous trial [25] we assume that the intra-cluster correlation coefficient will be 0.14 in the intervention arm and 0.09 in the control arm here, and based on our exploratory work we assume that we will be able to collect at least 500 eligible prescriptions per township hospital during the trial period, which we assume as our fixed cluster size. Based on these assumptions we estimated that we will require 17 clusters per arm to detect a 15-percentage-point or greater absolute reduction in the APR with 80% power using a two-sided hypothesis test with an alpha of 0.05 [37]. Because our previous trial data indicated potentially important county-level differences in baseline and during-trial-period APR levels and in the magnitude of the treatment effect, we also plan to stratify our randomisation by county. Therefore, this sample size also accounted for an unequal allocation ratio within strata, and, specifically given the number of clusters available in each county, it accounted for a within-county intervention-to-control allocation ratio of 8:9, which we chose in favour of the control arm for logistical purposes.

### Recruitment, randomisation and blinding

We will select and seek to recruit all eligible township hospitals and their associated village clinics (i.e. clusters) in the two study counties. There are 17 eligible township hospitals in Lechang county and 17 in Nanxiong county, but we will exclude the two township hospitals from Nanxiong county that will be part of the pilot (see below). We will seek written informed consent from the director of each township hospital on behalf of family physicians in township hospitals and the use of their EMR data. We will also seek written informed consent from all village doctors when participating in the initial training session. We will collect de-identified patient prescriptions from routine EMR system, so individual patient consent is not necessary. Following recruitment the study statistician ([name]) will randomise all recruited township hospitals at the same time, stratified by county, to the intervention or control arm in an overall 1:1 ratio, but will use an 8:9 intervention-to-control-arm ratio within each county, using a simple custom-written computer program in R [38]. Township hospital family physicians and village doctors in the intervention group will then be invited to attend the training.

As the intervention will be applied at the cluster level all patients visiting township hospitals during the trial period will receive the treatment allocated to their cluster. Due to the nature of the intervention it will not be possible to blind providers or patients/caregivers to treatment allocation. However, we will blind the assessors of the adverse events’ outcome (see below), while all other data will be collected from routine databases, and we will also blind the data analysts.

### Data collection and management

#### Clinical consultations and prescriptions

In township hospitals a prescription is required for each consultation to record the clinical visit to enable patients to receive reimbursements from the rural health insurance scheme. Therefore, although in theory patients may visit a family physician but not obtain a prescription this is rare in practice because patients do not feel that they are ‘being taken care of’ without receiving medication(s) [39]. Also, even when outpatient visit costs are not covered by the health insurance scheme patients still prefer to register their visits because the scheme covers much of their consultation costs [40].

#### Primary and secondary outcomes

Following the baseline and the trial periods we will extract all eligible patient prescription data from the EMR for all township hospitals. The Prefecture Health Information Centre manages all EMR, and will provide encrypted and de-identified electronic prescription data (e.g. names, addresses and health insurance numbers will not be collected). We will then clean the data and enter it into a standard format database to store all outcome and covariate data (including diagnoses, medicines prescribed, medicine and consultation costs, plus patients’ age, sex, insurance status, date of visit, any related treatments, payment details and any re-visit or hospitalisation data). We will also collect relevant covariate data from all township hospitals, including family physicians’ age, sex, experience and qualification level, which we can be link to each prescription via unique prescriber IDs.

To allow us to exclude patient prescriptions from outcomes where the patients have excluding comorbidities, we will also record any comorbidities as per secondary diagnoses shown on prescriptions. We will also check medications listed on prescriptions to link them to possible diagnoses. For example, steroid inhalers with asthma or chronic obstructive pulmonary disease, anti-diabetic medications with diabetes, and anti-hypertensive medications with hypertension. The Prefecture Health Information Centre will use the encrypted personal health insurance numbers in each prescription to identify any long-term comorbidities recorded such as diabetes, hypertension, cardiovascular disease. We will also develop a list of keywords used locally in prescription diagnoses for respiratory infections (which are often symptom based), and will manually screen and code all prescriptions not containing an ICD-10 code of diagnosis.

#### Patient safety indicators

We will collect all inpatient charts from the EMR managed under the Prefectural Health Information Centre for any patients who are hospitalised (in any hospital within the Shaoguan Prefecture, including its county and prefectural-level teaching hospitals) within 30 days of their index visit to a trial township hospital for an ARI or for sepsis. The Prefectural Health Information Centre will provide de-identified patient charts for review after identifying patients as having visited a trial township hospital within 30 days of becoming hospitals, using patients’ encrypted insurance numbers. We will then have these inpatient charts reviewed by a group of three to five physicians (blinded to the township hospital of all patients) who will decide if the hospitalisation is due to one of the following reasons: (1) not providing antibiotics during the index visit; (2) other inappropriate usage of antibiotics, such as prescribing the wrong antibiotics; (3) side-effects from antibiotics or other medications and (4) undetermined. Any patients who are determined to have been hospitalised due to either the first or second of these reasons will be included in the calculation of the adverse events’ outcome.

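### The panel-attributed adverse-event count has no stated rank beside the hospitalisation rate, and its two counted reasons depend on the prescribing that the intervention changes

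*Protocol article*

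**What the plan says.** The subsection Patient safety indicator, under Outcomes, sets out to detect harm "by creating and evaluating an indicator of unintended harms". Its example is harm arising "because of antibiotics being withheld for appropriate conditions more frequently due to the intervention". It then defines a "cluster-level hospitalisation rate for trial participants as the number of hospitalisations for respiratory infections or sepsis per 100 outpatient consultations", restricted to admissions within 30 days of the index visit. No judgement of cause is involved. The subsection ends: "We will compare both patient safety indicators between treatment arms". Only one indicator has been defined by that point.

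The subsection Patient safety indicators, under Data collection and management, adds a second step. Three to five physicians, blinded to township hospital, review the inpatient charts and assign each admission to one of four reasons. Two are counted: "1) not providing antibiotics during the index visit" and "2) other inappropriate usage of antibiotics, such as prescribing the wrong antibiotics". The other two, side-effects of antibiotics or other medications and undetermined, are not. The counting rule reads: "Any patients who are determined to have been hospitalised due to either the first or second of these reasons will be included" in the adverse-event outcome.

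Recruitment, randomisation and blinding refers to blinded assessors of the adverse-event outcome. The Discussion presents hospitalisation for respiratory infection or sepsis as the safety measure and does not mention attribution. Nowhere does the article say how the panel count relates to the rate, which of the two carries the safety conclusion, or what the count is divided by.

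**The concern.** A safety comparison between randomised arms should not move merely because the intervention changed prescribing. The panel count can. Each counted reason is defined by what happened with antibiotics at the index visit, and that is what the primary outcome measures and the intervention is meant to alter. Lowering the antibiotic prescription rate enlarges the group in which the first reason is possible and shrinks the group in which the second mainly arises, even if no patient's risk of admission changes.

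The count is also one-sided. Side-effect admissions, which less antibiotic use could reduce, are identified by the panel and then left out. There is no category for admission through the ordinary course of the illness; such cases must be called undetermined or put down to prescribing or side-effects.

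Under Secondary outcomes the article recognises a closely related problem: outcomes restricted to prescriptions containing an antibiotic form subgroups defined after randomisation, can be biased, and are therefore treated as exploratory. It attaches no such caution to the panel count. If that count were taken as the main safety result, the trial could report harm that did not occur, or reassurance that is not warranted.

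**Working it through.** **Inputs from the Sample size section.** Control antibiotic prescription rate (APR) 80%; reduction of 15 points, giving 65%; intra-cluster correlation 0.09 (control) and 0.14 (intervention); 500 prescriptions per cluster; 17 clusters per arm; 80% power; two-sided alpha 0.05. The article gives no figure for the safety outcome.

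**Reproducing the plan's own figure.** This confirms that 80% v 65% is the planning contrast.

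- Control variance term: 0.80 × 0.20 × (0.91/500 + 0.09) = 0.01469.
- Intervention variance term: 0.65 × 0.35 × (0.86/500 + 0.14) = 0.03224.
- Clusters per arm: (1.96 + 0.842)² × (0.01469 + 0.03224) / 0.15² = 16.4, rounded up to 17, as stated.

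**Who can be counted, as a share of visits.**

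- Reason 1 (no antibiotic given): 1 − 0.80 = 20% control, 1 − 0.65 = 35% intervention; ratio 0.35/0.20 = 1.75.
- Reason 2 (mainly antibiotic given): 80% control, 65% intervention; ratio 0.65/0.80 = 0.81.

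**Ratio of the panel count when nothing differs in truth.** Let admission risk be equal in both arms and unrelated to antibiotic receipt. Let the panel assign reason 1 to a share a of admissions among patients given no antibiotic, and reason 2 to a share b among those given one. The admission risk cancels:

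ratio = (0.35a + 0.65b) / (0.20a + 0.80b)

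The numerator exceeds the denominator when 0.15a > 0.15b. So the ratio is above 1 if a > b, below 1 if a < b, and exactly 1 only if a = b. The shares below are assumptions, since the article gives none.

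| a | b | Intervention / control | Ratio |
|---|---|---|---|
| 30% | 0% | 0.105 / 0.060 | 1.75 |
| 20% | 2% | 0.083 / 0.056 | 1.48 |
| 30% | 5% | 0.1375 / 0.100 | 1.38 |
| 30% | 10% | 0.170 / 0.140 | 1.21 |
| 30% | 30% | 0.300 / 0.300 | 1.00 |
| 10% | 30% | 0.230 / 0.260 | 0.88 |

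The unattributed rate has ratio 1.00 in every row. At an assumed 1 admission per 100 visits and 17 × 500 = 8,500 visits per arm, it compares 85 with 85 admissions.

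**Two variations.**

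- Counting side-effects as well, at a share of 5% of admissions among antibiotic recipients, moves the 30%/5% row to (0.1375 + 0.0325) / (0.100 + 0.040) = 1.21. At a 10% share, the 30%/10% row moves to (0.170 + 0.065) / (0.140 + 0.080) = 1.07.
- If training also halved reason-2 attributions in the intervention arm, the 30%/10% row becomes (0.105 + 0.0325) / 0.140 = 0.98.

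**Blinding.** Reviewers do not know the hospital, but they must know whether an antibiotic was given at the index visit to assign reason 1. The mechanism works through that fact, so concealing the hospital leaves the arithmetic unchanged.

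**The case against.** The strongest reply is that the article already has two indicators. The closing sentence of the Outcomes subsection speaks of two, the Data collection heading is plural, and different names are used for the hospitalisation rate and the adverse-event outcome. On that reading the unattributed rate is compared between arms and would expose a spurious difference in the panel count. This stands. A reader might infer that the two sections contradict each other; the text does not support that. What it supports is that the second measure is not introduced where the first is defined, and that neither is given precedence.

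Second, the calculation assumes panel error. If every admission put down to withholding really was caused by it, a higher count in the intervention arm would be the very harm the article sets out to find. This stands in part: the size of the distortion depends on how attribution falls in patients with and without antibiotics, and the article gives no basis for that. But a chart review cannot show what would have happened under the other prescribing decision, so some misattribution should be expected.

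Third, leaving out side-effects may be a deliberate choice of scope, since the stated aim is unintended harm. Charts are in any case collected only for respiratory-infection or sepsis admissions, so most side-effect admissions would not reach the panel under any rule. This limits what reporting reason 3 can add.

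Fourth, one patient's prescription does not reveal the arm: on the planning figures 65% of intervention visits still receive an antibiotic and 20% of control visits do not. Blinding to hospital is therefore worth keeping.

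**Conclusion.** The point holds as a weakness in how the safety measures are specified and how the panel count can be interpreted. The counting rule and the missing rank, denominator and link can be read directly from the article. The pool ratios of 1.75 and 0.81 follow from its own APR figures, taking reason 2 as confined to antibiotic recipients. The resulting range of 0.88 to 1.75 for the count under equal admission risk rests on assumed attribution shares.

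A reader might infer that the count is always inflated against the intervention, by as much as 1.75. The documents do not support this: reason 2 works in the opposite direction, 1.75 requires that reason 2 is never assigned, and the net sign is unknown. A reader might also suppose that the Holm adjustment would blunt the safety comparison. The Statistical analyses section states Holm for the secondary outcomes, and the safety indicator stands under its own heading, so that does not follow.

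The matter affects what the trial can conclude about safety. It leaves the primary analysis untouched. It should be settled before the analysis plan is final, but it is not a defect that invalidates the design.

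**What to change.** State in the Outcomes subsection that there are two safety measures, and define both there.

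1. Between-arm safety comparison: all respiratory-infection or sepsis hospitalisations within 30 days, without attribution, per 100 eligible index consultations, reported with the between-arm difference and its 95% CI.
2. Supporting description: the number of admissions assigned to each of the four panel reasons, by arm, side-effects included and with a stated denominator. Label these descriptive or exploratory, with the same caution about dependence on post-randomisation prescribing that the article applies to its antibiotic-only secondary outcomes. Optionally add a category for disease course unrelated to the antibiotic decision.

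Align the Patient safety indicator subsection, the Patient safety indicators subsection and the reference to the adverse-event outcome under Recruitment, randomisation and blinding, so that each names the same measure in the same words. Keep the panel blinded to hospital.

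The cost is wording in the protocol and analysis plan and, if the extra category is adopted, one more line on the review form. The data are already to be collected and no further reviewers are needed.
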